### Trial design {8}

This is a pilot, parallel, partially nested randomized controlled trial (RCT) comparing two arms: intervention (M3) and waitlist control (i.e., treatment as usual). Participants will be randomized 1:1 into the intervention or control arm. This study will not interfere with patients’ clinical care. The intervention will be delivered online to groups of 4–8 on a rolling basis to minimize wait times and allow for timely access to the intervention for the waitlist controls.

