#### Sample size {14}

The sample size calculation was based on the results of our pan-Canadian prospective cohort study of children (aged 4–12 years) with newly diagnosed epilepsy [45]. Two years after diagnosis, we observed the mean score on the QOLCE-55 to be 76.4 with a standard deviation of 14.5. To our knowledge, there are no estimates of minimal clinically important difference (MCID) for the QOLCE-55, and no intra-class coefficient estimates available for the impact of group-based psychological interventions in CWE. We therefore assumed a conservative ICC among participants in M3 of 0.10, an average cluster size of 6, and aimed to detect a large effect size (*d* = 0.8) [62], corresponding to a 11.6-point difference on the QOLCE-55 between the two study arms. The 11.6 point difference is in line with the MCID found for the adult equivalent HRQOL measure, the QOLIE-31 [44]. Using the method for a trial with a group-administered intervention, a control arm with independent subjects, and 1:1 randomization [63], the study requires 38 child-parent dyads in the intervention arm and 38 child-parent dyads in the control arm to have 80% power and the 2-sided 5% significance level. We will aim to recruit 100 child-parent dyads to account for a liberal estimate of 24% attrition.

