### Statistical methods

#### Statistical methods for primary and secondary outcomes {20a}

Descriptive statistics will be run with continuous variables summarized using means and standard deviations and categorical variables summarized using frequencies and proportions. To evaluate study feasibility, descriptive statistics will be used to summarize study procedures among all participants, including (a) number of families contacted, (b) participation rate, (c) reasons and/or barriers for non-participation, (d) attrition rate, (e) time to complete questionnaires, and (f) missing data on questionnaires. To evaluate (1) participant feedback and adherence to M3 and (2) intervention fidelity, data from the intervention and control arms will be combined and descriptive statistics used to describe responses to the Weekly Parent Questionnaire, Parent Pre-Post Assessment, and Child Pre-Post Assessment, M3 Adherence Checklist, and Quality of Implementation questionnaire.

To evaluate Efficacy Outcomes (e.g., HRQOL), we will use linear mixed models, which are suitable for group-administered interventions to account for the clustering in the intervention arm and no clustering in the control arm [63, 64]. The primary interest will be comparing the mean scores of the intervention and control arms at the Immediate Follow-up (e.g., HRQOL 1-week post-M3), adjusting for potential imbalance at Baseline (e.g., HRQOL pre-M3). Given that age group (younger vs. older) was a variable used in stratifying randomization, analyses will adjust for age group.

Similarly, generalized linear mixed models will be used to evaluate whether the intervention and control arms differ with respect to the proportion who show clinically significant improvement, and the proportion with clinically elevated symptoms post-intervention [65].

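### For the binary outcomes, a logit mixed model with a group effect in the M3 arm only would not give an odds ratio of 1 when the two proportions are equal; the shift is small and its direction depends on prevalence

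*Protocol article*

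**What the plan says.** Trial design {8} describes a "pilot, parallel, partially nested randomized controlled trial". Statistical methods {20a} accordingly chooses linear mixed models for the efficacy scores, to "account for the clustering in the intervention arm and no clustering in the control arm".

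The same section then moves to binary outcomes, with the word *similarly* tying them to the linear models: "generalized linear mixed models will be used to evaluate whether the intervention and control arms differ with respect to the proportion who show" significant clinical improvement. The other binary outcome is "the proportion with clinically elevated symptoms post-intervention".

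The article names no link function for these models. It does not say whether the arm coefficient or a contrast of predicted proportions will be reported, and it gives no planning proportions for the binary outcomes. The only ICC is in Sample size {14}: "We therefore assumed a conservative ICC among participants in M3 of 0.10, an average cluster size of 6". That figure was set for the QOLCE-55 score, not for a binary outcome.

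**The concern.** In a linear model, a group effect with mean zero in one arm leaves the difference in means unchanged, so the partially nested structure does no harm. On the logit scale this no longer holds. The M3 coefficient describes a group whose random effect is zero, which is a conditional log-odds. The control arm has no random effect, so its log-odds are marginal. The arm coefficient is the difference between these two unlike quantities.

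This goes beyond the familiar gap between conditional and marginal odds ratios. When both arms carry the same random effect, the two odds ratios differ in size but both equal 1 under equal proportions. With the random effect in one arm only, the null value itself moves. The stated question is whether the proportions differ, and this coefficient does not exactly answer it.

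At stake is the accuracy of secondary estimates. The Discussion says the trial's data should improve estimates of the intervention's impact and support sample size calculations for a larger trial, so a systematic shift deserves attention even where no test is affected.

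**Working it through.** **The plan's own figure.** Sample size {14} gives a "mean score on the QOLCE-55 to be 76.4 with a standard deviation of 14.5", and d = 0.8, "corresponding to a 11.6-point difference on the QOLCE-55 between the two study arms", with 38 dyads per arm "to have 80% power and the 2-sided 5% significance level".

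- Difference: 0.8 × 14.5 = 11.6.
- Without clustering: n = 2 × (1.96 + 0.8416)² / 0.8² = 24.5, so 25 per arm.
- Design effect: 1 + (6 − 1) × 0.10 = 1.5.
- Design effect in the M3 arm only, with a Satterthwaite t test: 36 per arm if total variance is equal in both arms, 39 if residual variance is equal. The stated 38 lies between them.
- Attrition: 76 / (1 − 0.24) = 100.

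The sample size reproduces. It concerns QOLCE-55 means and is not touched by this point.

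**Inputs for the binary check.** ICC 0.10 comes from Sample size {14}. The logit link, the latent-scale reading of the ICC and the prevalences are assumptions. The nearest figures in the article are background rates in {6a}: up to 50% of mothers at risk for depression and 58% of parents at risk for anxiety.

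**Null value of the arm coefficient.** With latent-scale ICC ρ, the group variance is s² = ρ/(1 − ρ) × π²/3 = 0.10/0.90 × 3.290 = 0.366. Let p be the true proportion in both arms. The M3 intercept η solves E[expit(η + u)] = p with u ~ N(0, s²). The control intercept is logit(p). The arm coefficient at equal proportions is η − logit(p), found by 80-point Gauss–Hermite quadrature. A second-order expansion, −(s²/2)(1 − 2p), allows a check by hand.

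| p (both arms) | logit(p) | η | coefficient | by hand | OR |
|---|---|---|---|---|---|
| 0.10 | −2.197 | −2.339 | −0.142 | −0.146 | 0.87 |
| 0.20 | −1.386 | −1.490 | −0.104 | −0.110 | 0.90 |
| 0.30 | −0.847 | −0.916 | −0.068 | −0.073 | 0.93 |
| 0.40 | −0.405 | −0.439 | −0.034 | −0.037 | 0.97 |
| 0.50 | 0 | 0 | 0 | 0 | 1.00 |
| 0.58 | 0.323 | 0.350 | +0.027 | +0.029 | 1.03 |
| 0.70 | 0.847 | 0.916 | +0.068 | +0.073 | 1.07 |

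**Sensitivity to the ICC.** At p = 0.10, 0.20 and 0.30 the null odds ratio is:

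- latent ICC 0.05: 0.93, 0.95, 0.97;
- latent ICC 0.20: 0.74, 0.80, 0.87;
- ICC 0.10 read on the proportion scale: 0.67, 0.83, 0.90.

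**Against sampling error.** Trials were simulated with equal proportions, latent ICC 0.10, a maximum-likelihood logit model with a random intercept in M3 only, a Wald test and no covariates.

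- 6 groups of 6 against 38 controls, p = 0.30: SD of the estimate 0.66, so the shift is 0.068/0.66 = 0.10 SD. Rejections were 3.2% with the coefficient below zero and 2.0% above (2,000 runs).
- 8 groups of 6 against 50 controls, p = 0.30: SD 0.53, shift 0.13 SD, rejections 2.1% and 2.1% (6,000 runs).
- Same size, p = 0.20: SD 0.65, shift 0.104/0.65 = 0.16 SD, rejections 1.5% and 1.6%.
- 200 groups of 6 against 1,200 controls, p = 0.30: SD 0.107, rejections 10.0% below zero and 0.3% above (300 runs).

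Total type I error is at or below about 5% at the planned size. The asymmetry becomes plain only in a far larger trial.

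**The case against.** The strongest reply is that the article does not commit to the analysis that fails. It names no link, no odds ratio and no reported contrast, and these details may sit in an analysis plan that is not shown. Averaging predicted probabilities from a mixed model fits the text as written, and an identity link would remove the problem. Even with a logit link, each control could be coded as a cluster of one sharing the M3 group variance. Both arms are then conditional, and equal proportions give an odds ratio of 1.

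All of this stands, which is why the point is conditional. What remains is that the text carries the one-arm structure over to the binary outcomes, and the most customary implementation would not test equality of the proportions it names.

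A reader might also infer that the method favours M3 on elevated symptoms. The documents do not support that. Below 50% prevalence the shift does favour M3 on elevated symptoms, but it goes against M3 on improvement. It is zero at 50% and reverses above it. The article's own background rates are up to 50% and 58%, where the null odds ratios are 1.00 and 1.03.

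Nor does the evidence support a claim of inflated type I error at this trial's size. These are secondary outcomes of a feasibility pilot whose main interest is in mean scores, and the mean comparisons are unaffected.

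**Conclusion.** The point holds as a minor one. If a logit link is used with a random effect in the M3 arm only, the arm coefficient at equal proportions is not zero unless prevalence is 50% or the group variance is zero. At the planned ICC the null odds ratio is about 0.87 to 0.93 for prevalence 10% to 30% and 1.03 to 1.07 for 58% to 70%. This is a modest distortion of secondary estimates meant to inform the later trial, with no consistent direction and no effect on overall error rates here.

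The size rests on applying an ICC set for QOLCE-55 to the latent scale of a binary outcome, on assumed prevalences, and on simulations without the age-group and baseline covariates. A larger group variance would enlarge the shift.

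**What to change.** In {20a}, state that the binary comparisons target the difference in marginal proportions between arms. Report the adjusted risk difference with 95% CI in place of the raw mixed-model arm coefficient. Obtain it by averaging the M3 predicted probabilities over the fitted group-effect distribution before contrasting them with control, or from an identity-link partially nested model. GEE also targets marginal proportions but is debatable with so few groups and should not be the lead option.

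The cost is one sentence in {20a} and a few lines of code, with no new data. The drawback is slightly more analysis work, and the group variance over which the predictions are averaged will be poorly estimated with few groups.

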#### Interim analyses {21b}

There will be no interim analyses.

#### Methods for additional analyses (e.g., subgroup analyses) {20b}

Two sensitivity analyses are planned. First, to evaluate whether outcomes at the Immediate Follow-up (1 week post-M3) are retained or changed over the longer term (10-weeks post-M3), linear mixed models will be used to evaluate outcomes at each time point (Baseline, Immediate Follow-up, Extended Follow-up) for participants randomized to the intervention arm. Second, we do not plan to adjust for any covariates (other than age group and the value of the outcome variable at baseline), but may consider adjusting for variables that are substantively imbalanced between the study arms within the sensitivity analyses.

Lastly, adverse events will also be evaluated. Data from the intervention and control arms will be combined and descriptive statistics will be used to evaluate the frequency of adverse events, based on parents’ reports at the start of each M3 session. All collected adverse events will be reported.

#### Methods in analysis to handle protocol non-adherence and any statistical methods to handle missing data {20c}

Analysis will follow the intention-to-treat principle. We do not plan to impute missing values, but may consider use of multiple imputation or other strategies within the sensitivity analysis.

#### Plans to give access to the full protocol, participant-level data, and statistical code {31c}

The current document outlines the full protocol. Non-identifiable data may be made available in response to a reasonable and well-motivated request to the principal investigator. Data cannot, however, be made freely available to the public, due to privacy regulations and informed consent. A data sharing agreement will also need to be signed.

### Oversight and monitoring

#### Composition of the coordinating center and trial steering committee {5d}

The research team is multi-disciplinary, spanning epidemiology (KNS, KP), biostatistics (GZ, KP), pediatric neurology (AA, CC, MDR, HG, SL, MNN, ANP), clinical psychology (KB), and knowledge translation (MS). The immediate trial team (KS, KB, KP, and research coordinators) will oversee all aspects of the study, such as internal monitoring of the trial data and training of staff. The immediate trial team meets weekly or more frequently as needed to oversee the project and monitor progress. KB, a clinical psychologist, will be automatically made aware (via REDCap notifications) of any adverse events reported by parents and, if needed, will contact and follow-up with participants.

#### Composition of the data monitoring committee, its role and reporting structure {21a}

The immediate trial team (KS, KB, KP, and research coordinators) meets weekly or as needed to oversee the project and monitor progress. The main goal will be to evaluate study procedures and identify the need for any adjustments (such as recruitment procedures). Given that adverse events, if any, are expected to be minimal, an independent data monitoring committee was not deemed necessary.

#### Adverse event reporting and harms {22}

As indicated previously, adverse events, if any, are expected to be minor. At the start of each M3 session parents will be asked whether they experienced any physical discomfort, emotional discomfort or distress, or an increase in problems in relationships with others, while practicing any of the M3 skills in the past week. Parents will also be asked if their child experienced any unwanted negative events while practicing any M3 skills in the past week. KB, a clinical psychologist, will be automatically made aware of any adverse events reported by parents and, if needed, will contact and follow-up with participants. With respect to reporting adverse events, data from the intervention and control arms will be combined and descriptive statistics will be used to evaluate the frequency and severity of adverse events. All collected adverse events will be reported.

#### Frequency and plans for auditing trial conduct {23}

No audits have been planned. The immediate trial team (KS, KB, KP, and research coordinators) meets weekly or as needed to oversee the project and monitor progress.

#### Plans for communicating important protocol amendments to relevant parties (e.g., trial participants, ethical committees) {25}

Version control using protocol identifies and dates will be used. The research ethics board will approve amendments and substantive changes will be noted on clinicaltrials.gov and/or subsequent journal publication(s).

##### Past protocol versions

This manuscript is based on protocol version 3.0. In Version 3.0, the intervention was modified to be delivered interactively online, as a result of the COVID19 pandemic. Twelve participants were randomized prior to protocol version 3.0 and participated in the in-person intervention. Data from these participants will not be combined with future participants who complete the intervention online. A new randomization list was generated for participants participating in the online intervention, and a total of 100 will be randomized.

In Version 2.0, the operational process was modified for a pragmatic reason to increase the pool of participants waiting to receive the intervention and thereby expedite the time it takes to fill each group (as described in section “Participant timeline {13}”). The original process (in Version 1.0) was more restrictive and used a stringent timeline, requiring that the intervention arm receives the intervention in weeks 1–8 and the control arm receives the intervention in weeks 10–17. This limited the participant pool because eligible participants had to be available during weeks 1–8 and weeks 10–17 (given that they could have been randomized to either group).

#### Dissemination plans {31a}

We will develop a publication and dissemination plan to include conference presentations and journal publications. We plan to write to all participants to inform them of the trial results. We will also plan dissemination to relevant patient and clinical interest groups.

## Discussion

This protocol describes a funded pilot RCT evaluating the feasibility of implementing an interactive online mindfulness-based intervention for CWE and their parents. To the best of our knowledge, this is the first behavioral intervention targeting young children with epilepsy which is particularly important as evidence to date suggests that early identification and treatment of epilepsy comorbidities are essential as there may be a window of opportunity for early intervention in some children [66, 13]. Interventions must be implemented early before problems become entrenched and interfere with the development of basic cognitive, behavioral, and social skills crucial for long-term educational, vocational, and interpersonal adaptation. In addition, interventions (such as M3) targeting self-regulation and executive functioning may be most effective during the preschool and early school years given the ongoing brain development and maturation of children in this age group [67, 68]. M3 is also unique because the intervention is delivered to parents and children, providing parents and their child with a common vocabulary and skillset, and enabling them to jointly practice the skills learned. Lastly, we believe that this program provides an ideal vector to target the unmet mental health care needs of CWE and their parents, given that the program may be delivered by non-clinical staff and is delivered online in a group setting. These characteristics would allow the intervention to be implemented at low cost and by epilepsy support centers, allowing scalability to communities across the country and increasing its likely sustainability.

The primary goal of this RCT is to evaluate feasibility, with respect to participant adherence and the quality with which facilitators are able to implement the intervention. Additionally, the feedback received from the recruitment, randomization, retention, and assessment procedures, as well as the feedback from parents and facilitators will allow us to better implement this intervention in a subsequent, larger multicenter trial. The data collected will also allow for the calculation of the MCID in HRQOL scores and enable better estimates of the impact of the intervention on key outcomes. This information will be necessary for robust sample size calculations. In reaching these feasibility goals, this study will employ a short follow-up period, comparing the intervention and control arm immediately after the intervention. This short follow-up may make it difficult to identify significant improvements in HRQOL, which may take some time to develop. However, participants in the intervention arm will also report on outcomes 10 weeks after the intervention, to estimate a longer-term effect. Improvements in other domains, such as depression, anxiety, executive function, and stress, may be evident in the short term. Regardless, the information obtained from these measures will be essential in the development of our subsequently large-scale RCT.

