**Methods:**

This parallel RCT was planned to recruit 100 child-parent dyads to be randomized 1:1 to the 8-week intervention or waitlist control and followed over 20 weeks. The intervention, M3, will be delivered online and separately to parents and children (ages 4–10 years) in groups of 4–8 by non-clinician staff of a local community epilepsy agency. The intervention incorporates mindful awareness, social-emotional learning skills, and positive psychology. It is modeled after the validated school-based MindUP program and adapted for provision online and to include a parent component.

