### Objectives {7}

Our long-term goal is to improve the quality of life of children with epilepsy and their family. The objective of this pilot trial is to evaluate the feasibility of utilizing Making Mindfulness Matter (M3)© as a non-medical therapeutic, interactive online intervention for children with epilepsy and their parents. Our central hypothesis is that M3 will be successfully implemented and will improve HRQOL and overall mental health and well-being in CWE and their parents. We plan to test our central hypothesis and accomplish the overall goal of this trial by pursuing the following specific objectives:

Primary objective:
To assess the feasibility of successfully implementing Making Mindfulness Matter (M3)© as a live online family intervention for children with epilepsy (CWE) and their parents. Specifically, we will evaluate
Study procedures (e.g., recruitment, attrition, time to complete questionnaires),Participant feedback and adherence to M3,Intervention fidelity.

This information will be essential in preparing for a subsequent multi-centered trial across Canada. Feasibility outcomes will be evaluated throughout the course of the study, and the specific outcomes collected and evaluated are presented in section “Outcomes {12}”.

Secondary objectives are to obtain preliminary data regarding the impact of M3 on:
2.Children’s health-related quality of life (HRQOL);3.Parents’ HRQOL;4.Children’s (*i*) externalizing problems, (*ii*) internalizing problems, (*iii*) adaptive skills, (*iv*) executive function, and (*v*) severity of epilepsy; and5.Parents’ (*i*) depression, (*ii*) anxiety, and (*iii*) stress.

All secondary outcomes (i.e., efficacy outcomes) will be evaluated 0–2 weeks before the intervention (i.e., baseline), and 1-week after the intervention (i.e., immediate follow-up). Efficacy outcomes for the intervention arm will also be evaluated 10 weeks after the intervention (i.e., Extended Follow-up). The timeline of assessment is presented in Table 2 and section “Participant timeline {13}”.

**Table 2 Tab2:** Schedule of evaluations

	Pre-randomization		Post-randomization				
	Screening/consent	Baseline (week: *−1 to 0)*	Intervention *(weeks 1–8)*			Immediate follow-up *(week 9; 1 week post-M3)*	Extended follow-up *(week 18; 10 weeks post-M3)*
			Session 1	Sessions 2–7	Session 8		
Screening form	X						
Informed consent-parent	X						
Assent child			X^a^				
Clinician’s questionnaire		X					
Parent questionnaire							

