##### Control arm: waitlist control

Child-parent dyads randomized to the control arm will continue treatment as usual. They will complete the baseline and immediate follow-up questionnaire at comparable times to families in the intervention arm; they will not complete the Extended Follow-up questionnaire. These dyads will be provided with the intervention at the next scheduled session after they have completed the immediate follow-up; the goal is to provide the intervention to controls as soon as possible to avoid differential attrition between the intervention and control arm. During the intervention sessions, participants in the control arm will complete all feasibility questionnaires before and after each session, pertaining to the intervention and their satisfaction with each session.

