**Fig. 1 Fig1:**
[figure not shown]
Schematic of participant progress

Participants in the intervention arm will be asked to complete a similar questionnaire, the Extended Follow-up, 10 weeks after the end of the M3 session. For participants in the control arm, the Immediate Follow-up questionnaire is the final follow-up questionnaire they complete. To provide interested controls with the intervention as soon as possible, those interested in receiving the intervention will be placed in a queue and will be able to join the next scheduled M3 sessions. Therefore, M3 sessions may be composed of participants randomized to the intervention arm and/or controls who have completed the study (completed Baseline and Immediate Follow-up questionnaires). During the M3 sessions, all participants will complete the same online questionnaires pertaining to the content of the M3 sessions and their experience with the intervention. Once the intervention ends, those who were randomized to the control arm will not need to complete any follow-up questionnaires. Therefore, the role of the controls in the intervention would be to simply honor the commitment for everyone to receive the M3 sessions and to “fill” the group (given that 4–8 participants are needed per group). The advantage of including dyads randomized to intervention and dyads previously randomized to the control arm is that it will increase the pool of participants waiting to receive the intervention and thereby expedite the time it takes to fill each group. The other advantage is that it would ensure that dyads randomized to the control group will receive the intervention as soon as possible and ameliorate attrition in the control group.

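### The week-18 data exist only in the M3 arm, so they can describe that arm's course but cannot estimate a longer-term effect as the Discussion says

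*Protocol article*

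**What the plan says.** The schedule of evaluations (Table 2, under Objectives {7}) places the Extended Follow-up at "week 18; 10 weeks post-M3". Objectives {7} and Outcomes {12} both limit it to the intervention arm. For controls, the section on the waitlist arm says "they will not complete the Extended Follow-up questionnaire". Participant timeline {13} repeats this: "For participants in the control arm, the Immediate Follow-up questionnaire is the final follow-up questionnaire they complete". It adds that "those interested in receiving the intervention will be placed in a queue and will be able to join the next scheduled M3 sessions".

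The one analysis of the week-18 efficacy outcomes stands under Methods for additional analyses {20b}. It is listed as a sensitivity analysis: linear mixed models for outcomes "at each time point (Baseline, Immediate Follow-up, Extended Follow-up) for participants randomized to the intervention arm", to see whether the week-9 result is kept or changes.

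The Discussion gives the same data a larger purpose. It grants that a comparison one week after the programme may be too early to show gains in quality of life, and then answers that "participants in the intervention arm will also report on outcomes 10 weeks after the intervention, to estimate a longer-term effect". The section giving the rationale for the short follow-up takes a different line: long-term effectiveness is not the primary objective, and longer-term outcomes are left to a later large trial.

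**The concern.** In a trial of M3 against waitlist, an effect is a difference between randomised arms. At week 18 one arm has no data, and some of its members may already have started M3. What remains is a before-after change in treated families.

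The protocol itself names other sources of such a change. The Discussion cites ongoing brain development at this age. The outcomes are rated by parents who attended M3 and, under Who will be blinded {17a}, can hardly be blinded. Attrition of 24% is allowed for. Regression to the mean is a weaker candidate for the whole arm, since entry does not depend on a low score. It could still arise if families join when things are going badly, and more so in the planned subgroups by initial level.

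Two readings of the results are at stake: that a gain from baseline at week 18 shows a lasting effect, and that a flat course from week 9 to week 18 shows the effect was retained. Neither follows. The point carries more weight because the Discussion brings in the week-18 data exactly where it expects the randomised comparison to fall short, and calls the information essential for developing the next trial.

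**Working it through.** **The plan's own figure.** The plan gives no figure for week 18. Its sample size concerns the between-arm comparison and can be reproduced: 2 × (1.96 + 0.842)² / 0.8² = 24.5, so 25 per arm; design effect 1 + (6 − 1) × 0.10 = 1.5; 25 × 1.5 = 37.5, so 38 per arm; 76 / (1 − 0.24) = 100. (This short form puts the design effect on both arms. A partially nested calculation with a t reference and 2(k − 1) degrees of freedom, k being the number of groups, gives 80.8% power at 38.) Nothing in it supports a week-18 effect.

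**What can be estimated.** Let E9 and E18 be the effects of M3 at weeks 9 and 18, and U9 and U18 the changes from baseline that the same families would have had without M3.
- M3 arm, baseline to week 9: E9 + U9. The control arm estimates U9, so E9 can be separated out.
- M3 arm, baseline to week 18: E18 + U18. No control data estimate U18, so E18 cannot be separated out.
- M3 arm, week 9 to week 18: (E18 − E9) + (U18 − U9). An observed change of zero fits a fully retained effect with no drift. It fits equally well an effect that faded by 3 points against an untreated gain of 3 points.

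**How small a change would look significant.** Inputs: SD 14.5 (Sample size {14}); n = 38, the number required per arm, to n = 50, which means no attrition; design effect 1.0 to 1.5 (the upper value uses the plan's ICC of 0.10 and group size of 6, and assumes they carry over to change scores). The correlation r between the two time points is not in the documents and is assumed to be 0.6 to 0.8.

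Threshold for an observed mean change = 1.96 × 14.5 × √(2(1 − r)) × √(design effect / n).

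| r | n | SD of change | Threshold, design effect 1.0 | Threshold, design effect 1.5 |
|---|---|---|---|---|
| 0.6 | 38 | 12.97 | 4.12 | 5.05 |
| 0.7 | 38 | 11.23 | 3.57 | 4.37 |
| 0.8 | 50 | 9.17 | 2.54 | 3.11 |

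The range is about 2.5 to 5 points, less than half of the 11.6 points used for the sample size. With few groups, a t reference would raise these thresholds.

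**Chance of p<0.05 when M3 has no effect.** For n = 38, r = 0.5 to 0.8 and design effect 1.0 to 1.5, a true untreated drift gives a significant within-arm change this often: 1 point, 6 to 10%; 2 points, 11 to 27%; 3 points, 18 to 52%; 5 points, 41 to 92%. No document says what drift to expect.

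**The case against.** The strongest reply is that the analysis text does not make the claim. Methods for additional analyses {20b} asks only whether outcomes hold or change, and only in the M3 arm, which is a question about within-arm course. The word effect comes from one clause in the Discussion that governs no estimand, test or decision. Feasibility is primary and the efficacy objectives seek preliminary data. Each efficacy outcome has its primary interest at week 9, where Statistical methods {20a} also places the comparison of arms. All of this stands, and it limits the weight of the point. It does not correct the Discussion, which is at odds with the rationale for the short follow-up, and no section says that the week-18 change is uncontrolled.

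Four stronger readings are tempting, and the documents do not support them.
- A reader might infer that the trial plans to claim a lasting effect, or to test week 18 against baseline for significance. No such claim or test is specified; the risk is one of later interpretation.
- A reader might take 2.5 to 5 points as a drift that would make the result significant. It is the critical value for an observed change. A true drift of that size would reach p<0.05 only about half the time.
- A reader of the abstract, where dyads are "randomized 1:1 to the 8-week intervention or waitlist control and followed over 20 weeks", might think that controls are assessed throughout. Four sections of the article say otherwise, so this is loose wording. It changes no result, and neither does the sensitivity label.
- A reader might want the analysis limited to dyads seen at both times. That would discard partial data which the planned mixed model can use, and would make selective loss worse.

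Nor would giving controls the week-18 questionnaire repair the design, because some will have started M3 by then.

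**Conclusion.** The point holds as a mismatch between stated purpose and design. The Discussion promises an estimate of a longer-term effect, and the design yields only an uncontrolled change in the M3 arm. That follows from the article's own text and needs no assumption. An analysis plan that is not shown could not cure it, since it cannot supply control data.

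The numerical size is illustrative only. It rests on the plan's SD, an assumed correlation, a normal reference and a significance test that the plan does not specify. Under those assumptions an observed change of roughly 0.18 to 0.35 SD (2.54/14.5 to 5.05/14.5) would look significant without any contribution from M3. The randomised week-9 comparison is untouched. What changes is which conclusions the trial may draw beyond week 9.

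**What to change.** 1. Discussion: replace the clause about estimating a longer-term effect with wording such as *to describe the longer-term course within the M3 arm (uncontrolled)*. This also brings it into line with the rationale for the short follow-up.
2. Methods for additional analyses {20b}: keep the planned mixed model on all available M3-arm data. Report the mean changes from week 9 to week 18 and from baseline to week 18 with 95% confidence intervals, as description. State that efficacy claims rest only on the week-9 comparison between arms.
3. Secondary wording: call this an additional descriptive analysis rather than a sensitivity analysis, and say in the abstract that control assessments end at week 9.

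The cost is a few sentences of text and a stated limit on reporting. No visit, questionnaire or model changes. The longer-term claim becomes less favourable.
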